## Diagnostic work up

At the first visit of the patient at the outpatient clinic the study is discussed and information is handed out (day -5, see figure 1). During the initial oral inspection a diagnostic biopsy of the tumor is taken, in case no pathological conformation has been obtained already previously. During this phase patient is informed and signed Informed Consent obtained. A “diagnostic day” is scheduled in the standard workup, which routinely includes standard of care MRI and [^18^F]-FDG PET and, diagnostic CT neck, thorax and abdomen. [^18^F]BMS-986192 imaging is performed >24 h after or before [^18^F]-FDG PET (see below 3.3). Endoscopic examination with biopsies under general anesthesia (or if feasible in the outpatient clinic under local anesthesia) will be done after PET imaging (day 3±3, see figure 1) and additional biopsies of the tumor will be obtained. In case of discrepancies based on the [^18^F]-FDG and [^18^F]BMS-986192 uptake the patient will be asked for consent to additional biopsies.

## [^18^F]BMS-986192 and [^18^F]-FDG PET imaging acquisition

After inclusion and before panendoscopy, a [^18^F]BMS-986192 PET scan will be obtained for all patients. At VUmc, previous dynamic imaging with [^18^F]BMS-986192 has been performed to obtain data for kinetic modeling describing uptake, retention, and clearance of the tracer in tissue [58]. The steady state imaging timepoint for static whole body scanning has been set at 60-75 min after tracer injection. [^18^F]-FDG PET will be performed according to EANM guidelines [59]. To allow for ^18^F decay, [^18^F]-FDG PET and [^18^F]BMS-986192 PET will be performed with a minimum interval of 24 h time. PET-imaging will be done before panendoscopy (day 1 ±3, figure 1) and 21 days after nivolumab treatment (day 24±3, figure 1).

## Treatment with nivolumab

On day 3 ±3, patients will be treated with a single flat dose of 480mg IV. Details on preparation, handling and dispensing info are provided in section 5.6. Product description information is provided separately [32, 57].

## PET guided additional biopsies

Up to two additional biopsies will be taken when possible with acceptable additional risk in case the PET scan shows heterogeneous and/or discrepant uptake between tumor lesions of the same patient. In this way imaging [^18^F]BMS-986192 PET will aid further validation of PD-L1 IHC.

## Response evaluation

Patient will have a standard MRI of head and neck at screening (day -5-0, figure 1) and just before surgery (day 24 ±3-27, figure 1) to evaluate the response to nivolumab.

## Surgery

Primary tumor resection and (bilateral) cervical lymph node dissection with flap reconstruction will be performed after the immunotherapy. In general Dutch guidelines dictate that 80% of patients should start (surgical) treatment no later than 30 days after initial visit, depending on needed additional workup on the basis of e.g. PET-CT or to optimally prepare the patient for surgery. In preparation for surgery, special consideration must be taken when determining the resection margins- as nivolumab treatment may result in changes in tumor structure or volume. If deemed necessary by the operating surgeon, the tumor will be pre-operatively tattooed. The tattooed area will be removed during surgery. Furthermore, imaging with MRI is scheduled (see above) within 7 days before surgery to assess any changes. The immediate post-operative course lasts usually approximately 2 weeks during which hospital stay the patients will be monitored very closely for adverse events, including deviations from the usual recovery. Observations will be listed in the patient files. The tracheotomy cannula is normally removed on 5-7 days post-surgery.

## Post-surgery follow-up

Patients will be followed according to standard care during 12 months. The follow-up includes standard oral inspection and symptom directed physical examination. This will be combined with laboratory assessment to check for immune-related adverse events. In case the pathology report identifies tumor in the surgical margins and/or significant additional risk factors for recurrence, patients will continue treatment with (chemo)radiotherapy according to the Dutch Guidelines. Decision for additional treatment will be taken in the multidisciplinary tumor board. Additional treatments will be registered.

## Blood measurements: immunomonitoring and cytokine analysis

To ascertain if any relationship exists between observed PET image patterns and pre- and on-treatment immune status, polychromatic flowcytometric analyses of lymphoid and myeloid subsets in peripheral blood will be performed (for timepoints see section 7.11). Heparinized blood (40 ml) will be taken and PBMC isolated. The following 8-12 marker panels will be run on a BD LSRFortessa (with appropriate FMO controls): 1) Treg/effector T cell activation panel with among others: CD3, CD4, CD8, CD25, CD127, CD45RA, Ki67, FoxP3, CTLA-4, PD-1, CD27; 2) Dendritic cell panel: CD1c/BDCA-1, CD202/BDCA-2, CD141/BDCA-3, CD14, CD11c, CD16, CD19, CD40, CD80, PD-L1; 3) Myeloid-derived suppressor cell panel: CD11b, CD14, CD33, CD3/19/56 (Lin), HLA-DR, CD15, CD16, PD-L1. By performing these analyses at the indicated time points, we will gain unique insight in the kinetics of T cell activation following PD-1 blockade and pre- and on-treatment immune effector/suppressor subset profiles that may serve as biomarkers for clinical response and/or outcome, as we previously showed in a trial of combined ipilimumab and Prostate GVAX immunotherapy [60]. Plasma will also be stored and tested for cytokine content or seroreactivity at a later date.

## Plasma vesicle miRNAs

Exploratory blood-based biomarkers (plasma vesicle miRNAs) analysis will be performed. (for timepoints see section 7.11). Samples are immediately processed and plasma sample aliquots will be stored at -80°C until further exosome isolation and miRNA profiling.

## Tumor biopsy analysis

### Immunomonitoring: IHC

Tumor tissue from newly obtained FFPE material will be analyzed for PD-L1 (immunohistochemistry using the PDL-1 22C3 monoclonal antibody) and PD-1. Additional (in-house performed) investigational IHC analyses will include tumor and TIL PD-1 and PD-L2 expression, as well as explorative markers; CD3, CD4, CD8, FoxP3, IL10, MHC class I and II, and Ki67 double staining to ascertain effector T cell activation and proliferation in the tumor microenvironment as reported by [61].

### Genomic profiling

The DNA of biopsies of the surgical specimen will be analyzed for mutations and other genetic alterations by DNAseq and the number of neoantigens. DNA will be sheared by Covaris and we will use a SeqCap EZ HyperCap Workflow for library preparation. Paired end sequencing will be performed on an Illumina platform. Reads will be groomed and mapped to the human genome. Copy number profiles will be determined by QDNAseq [62] and somatic mutations will be called by a pipeline of four calling algorithms. RNAsequencing will be performed using the TruSeq RNA prepkit vs2 according to protocol and data analysed by routine pipelines at VUmc. Analysis of neoantigens will be performed with the neoantigen R package [63] and other algorithms using predefined cut-offs and in relation to the patient HLA subtype [64].

[figure not shown]
 Figure 1 Study Diagram for Patient

#

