We will perform extensive immune monitoring to assess baseline immune status as well as changes in immune cell infiltrate in tumor specimen prior to and after neo-adjuvant nivolumab using flow cytometry on single cell suspensions as well as six-parameter IHC staining on FFPE material. Similar analyses will be performed on surgically removed lymph nodes, as well as additionally obtained biopsies in case of heterogeneous result on baseline PET imaging). Additionally we will monitor changes in systemic immune responses by profiling peripheral blood at several time points during the treatment (as indicated), analysing frequencies and activation status of T cell subsets, peripheral blood dendritic cells and myeloid derived suppressor cells. We anticipate that we will find either pre-treatment immune traits or alterations in immune activation and immune infiltrate composition upon neoadjuvant nivolumab therapy.

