## Inclusion criteria

In order to be eligible to participate in this study, a subject must meet all of the following criteria:

1. Have a histologically confirmed diagnosis of locally advanced oral cancer (stage III/IV) which is planned for treatment with curative intent including surgical resection.
2. Be willing and able to provide written informed consent/assent for the trial.
3. Be ≥ 18 years of age on day of signing informed consent.
4. Must agree to provide tissue from fresh tumor biopsy pretreatment and from the surgical resection material to determine the actual PD-L1 status and perform immunomonitoring/DNA/RNA profiling.
5. Willing to allow up to two additional biopsies when baseline [^18^F]BMS-986192 PET /[^18^F]-FDG PET scans show heterogeneous and/or discrepant uptake.
6. Have a performance status of 0-1 on the ECOG Performance Scale ([Appendix 2](#_APPENDIX_2:_Eastern)).
7. Demonstrate adequate organ function as defined in table 1. All screening labs should be performed within 2 weeks before any study imaging procedures are performed.

Table 1 Adequate Organ Function Laboratory Values

| **System** | **Laboratory Value** |
| --- | --- |
| **Hematological** |  |
| White blood cell count (WBC) | ≥2,000 /mcL |
| Absolute neutrophil count (ANC) | ≥1,500 /mcL |
| Platelets | ≥100,000 / mcL |
| Hemoglobin | ≥9 g/dL or ≥5.6 mmol/L |
| **Renal** |  |
| Serum creatinine **OR**  Measured or calculated creatinine clearance  (GFR can also be used in place of creatinine or CrCl) | ≤1.5 X upper limit of normal (ULN) **OR**  ≥30 mL/min for subject with creatinine levels > 1.5 X institutional ULN |
| **Hepatic** |  |
| Serum total bilirubin | Total Bilirubin ≤ 1.5 x ULN (except subjects with Gilbert Syndrome, who can have total bilirubin < 3.0 mg/dL) |
| AST (SGOT) and ALT (SGPT) | ≤ 3 X ULN |

1. Women of childbearing potential (WOCBP) must use appropriate method(s) of contraception during the study and for 23 weeks after the last dose of nivolumab. Women who are not of childbearing potential (i.e. who are postmenopausal or surgically sterile) as well as azoospermic men do not require contraception ([Appendix 4](#Appendix4))
2. Men who are sexually active with WOCBP must use any contraceptive method with a failure rate of less than 1% per year. Men receiving nivolumab and who are sexually active with WOCBP will be instructed to adhere to contraception during the study and for 31 weeks after the last dose of nivolumab ([Appendix 4](#Appendix4)).

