## Secondary study parameters/endpoints

#### Heterogeneity analysis

#### Interpatient, intrapatient and intratumor SUV heterogeneity.

Correlation between both PET scans, and between imaging and response

The correlation between SUV for [^18^F]BMS-986192 and [^18^F]-FDG baseline and on treatment and early response evaluation with [^18^F]-FDG.

Correlation between PET data and Blood/Tissue markers

The correlation between continuous values as SUV and the categorical variables tissue PD-1 and PD-L1 IHC will be assessed for each tumor lesion. Correlation with immuno-monitoring analysis in tumor tissue/lymph nodes and blood, plasma vesicle miRNAs from blood, as well as DNA/RNA profiling in tumor tissue at baseline and at surgery will be assessed.

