## Tissue sampling

Baseline tissue sampling will be obtained at panendoscopy, and a second tissue sampling will be obtained at surgey (after nivolumab treatment). Tumor tissue biopsies from the primary tumor and (affected) lymph nodes obtained at panendoscopy or surgical resection will be formalin fixed and fresh frozen .

When the [^18^F]BMS-986192 PET scan show heterogeneous uptake between tumor lesions in individual patients, or [^18^F]BMS-986192 PET and [^18^F]-FDG show discrepant results, up to two additional biopsies are allowed, if the area can be safely reached. If these discrepant results pertain to an area of interest that is already determined for surgical resection, a titanium marker is allowed to be placed before surgery under ultrasound guidance, if the area can be safely reached. The procedure for marker placement resembles that of taking a biopsy and holds similar risk.

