|  | Nivolumab treatment |  |  |  |  |  |  |  |  |  |  |  |  |  | X | |  |  |  |  |  |
|  | **Laboratory Procedures/Assessments** |  |  |  |  |  |  |  |  |  |  |  |  |  |  |  |  |  |  |  |  |
|  | Pregnancy Test^6^ | X |  |  |  |  |  |  |  |  |  |  |  |  |  |  |  |  |  |  |  |
|  | Complete Blood Count (CBC) | X |  |  |  |  |  |  |  |  |  |  |  |  |  |  | X |  |  | X | X |
|  | Comprehensive Serum Chemistry Panel^7^ | X |  |  |  |  |  |  |  |  |  |  |  |  |  |  | X |  |  | X | X |
|  | **Tumor Tissue and Blood collection** |  |  |  |  |  |  |  |  |  |  |  |  |  |  |  |  |  |  |  |  |
|  | Tissue collection for genomic profiling |  |  | | | | | | | | |  | | |  |  |  |  |  | X^8^ |  |
|  | Tissue collection for Immunohistochemistry |  |  | | | | | | | | | X^8^ | | |  |  |  |  |  | X^8^ |  |
|  | Tissue collection for flow cytometry |  |  | | | | | | | | |  | | |  |  |  |  |  | X^8^ |  |
|  | Blood for Immunophenotyping and plasma vesicle miRNA’s |  | X^9^ | | | | | | | | |  | | |  | | X | X^9^ | |  | X^10^ |
|  |  |  |  |  |  |  |  |  |  |  |  |  |  |  |  |  |  | |  |  |  |
|  | Standard of Care |  |  |  |  |  |  |  |  |  |  |  |  |  |  |  |  | |  |  |  |
|  | Study procedure |  |  |  |  |  |  |  |  |  |  |  |  |  |  |  |  | |  |  |  |

1. Follow up will end 12 months post-surgery, or earlier when withdrawing consent, becoming lost to follow-up or at the start of new anti-neoplastic therapy.
2. [^18^F]BMS-986192 PET and [^18^F]-FDG PET need to occur with an interval of min. 24h.
3. Only if diagnosis has not been histologically confirmed at presentation
4. This includes AEs, SAEs and SUSARs, as described in section 8.1
5. Adverse events will be monitored until 100 days after nivolumab treatment.
6. Only for women of childbearing potential.
7. This includes Albumin, Akaline phosphatase, Alanine aminotransferase (ALT), Aspartate aminotransferase (AST), Lactate dehydrogenase (LDH), Amylase, Lipase, Creatinine, Calcium, Glucose, Phosphorus, Potassium, Sodium, Chloride, Magnesium, Total Bilirubin, Free Thyroxine (T4), Triiodothyronine (T3), Thyroid Stimulating Hormone (TSH). 1 tube of 6ml EDTA (EK) and one tube of 6ml Heparin Gel (HG) need to be collected.
8. Tissues are collected during standard procedures.
9. Blood is to be withdrawn before [18F]-BMS-986192 administration.

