## Correlation between PET data and response

The correlation between the continuous variable SUV, the % change in SUV and TLG and the categorical variables response on imaging (according to RECIST 1.1 CR, PR, SD, PD and CMR, PMR, SMD and PMD according to PERCIST) and pathological response (according to the Mandard Classification System, Table 3) will be assessed.

**Table 3** Mandard Classification system for Tumor Regression Grading (TRG) [69, 70]

| **Descriptive** |  |  |
| --- | --- | --- |
| Complete regression | TRG 1 | No residual cancer cells |
| Subtotal | TRG 2 | Rare cancer cells |
| Partial | TRG 3 | Fibrosis outgrowing residual cancer |
| No regression | TRG 4 | Residual cancer outgrowing fibrosis |
|  | TRG 5 | Absence of regressive change |

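### Sections 3.10.2 and 7.19 assign tumor sequencing to the post-nivolumab surgical specimen only, contradicting 6.2 and inclusion criterion 4 and, if followed, tying missing genomic data to response

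*Protocol*

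**What the plan says.** Two places in the protocol decide which tumor tissue is sequenced, and both point to surgery.

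- Section 3.10.2 (Genomic profiling), the methods section for sequencing: "The DNA of biopsies of the surgical specimen will be analyzed for mutations and other genetic alterations by DNAseq and the number of neoantigens". It names no other tumor tissue.
- Section 7.19 (Schedule of assessments), row "Tissue collection for genomic profiling": the only mark is in the Surgery column. The next row, "Tissue collection for Immunohistochemistry", is marked at both Panendoscopy and Surgery.

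Two other places expect both time points.

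- Section 6.2 (Secondary study parameters/endpoints) lists correlation of the PET data with immune and blood markers, "as well as DNA/RNA profiling in tumor tissue at baseline and at surgery will be assessed".
- Section 4.1, inclusion criterion 4: "Must agree to provide tissue from fresh tumor biopsy pretreatment". The same criterion also asks for resection material and gives DNA/RNA profiling among the purposes of both samples.

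Section 7.16 (Tissue sampling) takes baseline tissue at panendoscopy and a second sample at surgery. Tumor and node biopsies "obtained at panendoscopy or surgical resection will be formalin fixed and fresh frozen".

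**The concern.** A laboratory working from 3.10.2 and 7.19 would sequence one tumor sample per patient, taken about three weeks after nivolumab, and would not deliver the baseline half of the 6.2 endpoint.

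Objective 6 relates neoantigens, mutational load, copy number and splice variants to tracer uptake, immune activation and clinical response. Its hypothesis, that checkpoint inhibition works best in tumors with a high mutational load, concerns the tumor as it was before treatment. Surgical tissue serves that question poorly in two ways.

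1. Under Table 3 in the section on correlation between PET data and response, TRG 1 means "No residual cancer cells", and TRG 2 leaves only scattered tumor cells. Whether a sample can be sequenced then depends on the outcome being analysed.
2. In the other patients the profile describes tumor that has persisted through treatment, which may differ from the tumor that was treated.

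Section 1.2.4 says the genomic work should show whether these methods add value in a larger randomized trial. Data that drop out in the best responders would weaken that judgement.

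**Working it through.** **Step 1. Set the texts side by side.**

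| Place | Baseline tumor tissue for DNA/RNA | Surgical tumor tissue for DNA/RNA |
| --- | --- | --- |
| 3.10.2 | not named | named |
| 7.19, genomic row | blank | marked |
| 6.2 | promised | promised |
| 4.1, criterion 4 | required | required |
| 7.16 | collected, fixed and frozen (no assay named) | collected, fixed and frozen (no assay named) |

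The immunohistochemistry row in 7.19 is marked at both visits, so the blank in the genomic row looks specific to that row. The germline blood sample in 7.11 is not a substitute, because it carries no tumor profile. So the baseline tissue is collected and preserved. What is missing is its assignment to sequencing.

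**Step 2. Timing.** In 7.19 nivolumab is on day 3 ±3 and surgery on day 25 ±4. The nominal gap is 25 − 3 = 22 days, so surgical tissue is on-treatment tissue.

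**Step 3. Reproduce the plan's own figure.** Section 1.1.2 anticipates at least 3-4 histopathological responders among 15 patients, about 25%.

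- Expected number: 15 × 0.25 = 3.75.
- 3/15 = 20.0% and 4/15 = 26.7%, so the figure holds as an expected count.
- At a true rate of 25%, the binomial probability of at least 3 responders is 0.76, and of at least 4 is 0.54.

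**Step 4. What surgery-only sequencing could lose.** If k of R responders have no usable tumor in the specimen, the share lost is k/R.

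- k = 0: no loss.
- k = 1, R = 4: 1/4 = 25%, leaving 3 responders.
- k = 1, R = 3: 1/3 = 33%, leaving 2 responders.

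**Step 5. How likely is any TRG 1 patient?** The protocol gives no TRG 1 rate, so p below is an assumption. The chance of at least one among 15 is 1 − (1 − p)^15.

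| Assumed TRG 1 rate p | Expected number, 15p | Chance of at least one |
| --- | --- | --- |
| 2% | 0.3 | 26% |
| 5% | 0.75 | 54% |
| 10% | 1.5 | 79% |

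The protocol also does not say which TRG grades make up the anticipated response. If all the responders were TRG 3, the loss from this cause could be zero.

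**Step 6. Sequence the panendoscopy biopsy as well.** TRG 1 then causes no loss of the baseline profile, and all 15 patients can contribute one, subject to biopsy yield.

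**The case against.** The strongest reply is that this is an inconsistency and not a settled surgery-only design. Criterion 4 obliges every patient to give pretreatment tissue for profiling, 7.16 preserves it, and section 3 describes collecting specimens before and after treatment. That reply stands. A reader might infer from 3.10.2 that the baseline profile cannot be made, but the tissue exists in suitable form and has simply not been assigned.

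The reply on consequences also carries weight. Objective 6 is secondary, section 4.3 calls the study descriptive and hypothesis generating, and 1.2.4 concedes that strong associations cannot be found with this number of patients. No primary objective depends on it. This limits the severity but leaves the contradiction in place.

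Three further inferences are tempting and are not supported:

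- **That genomic data will be missing in every complete responder, or in most responders.** This requires the surgery-only reading plus an assumed TRG rate. No minimum tumor content is set, so TRG 2 tissue may be usable, and resected nodes may still hold tumor when the primary has regressed.
- **That objective 6 is tied to uptake on the baseline scan.** It names tracer uptake without a time point. It also names immune activation, which is read partly in resection material, so surgical tissue does serve part of the objective.
- **That tumor flow cytometry has the same defect.** Section 1.2.3 speaks of "changes in immune cell infiltrate in tumor specimen prior to and after neo-adjuvant nivolumab using flow cytometry on single cell suspensions", and 7.19 schedules flow tissue at surgery only. But 1.2.3 names immunohistochemistry alongside, 1.2.7 assigns tumor immune status to immunostaining and flow cytometry to blood and draining nodes, and immunohistochemistry is scheduled at both visits. What remains is loose wording in a rationale section.

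**Conclusion.** The concern holds as a contradiction with a conditional consequence. Sections 3.10.2 and 7.19 restrict tumor sequencing to post-nivolumab surgical tissue, while 6.2 and criterion 4 require a pretreatment profile as well. The contradiction rests on the text alone and needs no assumption.

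If the surgery-only text is followed, the baseline part of the 6.2 endpoint is not produced, and missing or poor tumor data in objective 6 will depend on response. The size of that loss cannot be fixed from the protocol. It may be zero, and it is 25-33% of responders if one of the anticipated 3-4 is affected. That range assumes the plan's own responder count and that the affected patient has no sequenceable tumor elsewhere in the resection.

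This should be fixed. It does not rank higher, because the objective is secondary and exploratory and the tissue needed is already secured.

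**What to change.** - In 3.10.2, name the panendoscopy (pre-nivolumab) biopsy as a source for DNA and RNA sequencing, next to the surgical specimen.
- In 7.19, add a mark at Panendoscopy in the genomic tissue row.
- For objective 6, state that the baseline profile is the predictor of response and that the surgical specimen is the on-treatment comparison.

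No extra biopsy is needed, since 7.16 already provides the tissue. The cost is a protocol amendment and sequencing of up to 15 baseline samples. The drawback is that biopsy tissue is limited and shared with immunohistochemistry, so its division should be settled before the material is used.

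The alternative is to withdraw the baseline commitment from 6.2 and criterion 4. That removes the contradiction but leaves missingness that depends on response, which would then have to be stated as a limitation of objective 6.
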